**Methods/design:**

This study is a three-arm, randomized controlled trial. A total of 105 patients will be randomized into a group receiving electroacupuncture at Tianshu (ST25), a group receiving electroacupuncture at Zusanli (ST36), or a control group in a 1:1:1 ratio. Patients in the electroacupuncture groups will receive electroacupuncture treatment for 4 days from the first day after surgery. The primary outcome consists of the time to first flatus and the time to first defecation. Secondary outcomes include the time to first tolerance of liquid and semiliquid food; the length of the hospital stay; postoperative pain, nausea, and vomiting; abdominal distension; the time to first get out of bed; and postoperative complications. The outcomes will be assessed by the patients themselves every day during hospitalization. Surgeons, nurses, assessors, and statisticians will be blinded to the group assignments. Patients in the two electroacupuncture groups, but not in the control group, will be blinded to the group assignments. The acupuncturists will not be blinded.

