### Masking

Patients in the two EA groups, hospital staff (surgeons and nurses) assessors, and statisticians will be blinded to the group assignments, but the patients in the control group will not be blinded because of the particularity of the treatment. The acupuncturists will not be blinded.

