#### Control group

Patients in the control group will receive RSPC without acupuncture. At the end of the trial, if a patient is willing to contact us, we will give free acupuncture treatment.

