### Primary outcome

The primary outcome is a composite endpoint consisting of the time to first flatus and the time to first defecation [34], which are defined as the time from the end of the operation to the first exhaust and defecation, respectively, and will be recorded in hours in the case report form by patients under the supervision of an assessor during hospitalization. The minimum clinical significance of the primary outcome is 12 h [27].

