### Secondary outcomes

Secondary outcomes will include the length of the hospital stay; the time to first tolerance of liquid and semiliquid food; postoperative pain; postoperative use of analgesics; postoperative nausea and vomiting; the time to first walk independently; postoperative distension of the abdomen; and adverse events.

The length of the hospital stay is defined as the time from the end of the operation to discharge. The time to first tolerance of liquid and semiliquid food is defined as the time from the end of the operation to the first tolerance of the aforementioned two kinds of food without gastrointestinal adverse reactions. The time to first walk independently is defined as the time from the end of the operation to the first time the patient can get out of bed and ambulate. Postoperative pain will be evaluated regularly at three fixed times per day using the visual analog scale (VAS, from 0 to 10), and the three scores will be averaged. The higher the score is, the more severe the indication of pain and nausea is. Vomiting, nausea, and abdomen distension will be counted once, daily. The abovementioned outcomes will be recorded by the patient on a daily assessment form (DSF) during hospitalization.

Adverse events include postoperative complications and adverse acupuncture events. Postoperative complications, such as fever, intestinal edema, and intestinal anastomotic fistula, will be recorded and graded according to the Clavien-Dindo classification (Table 2) by the assessors. If patients have serious complications after surgery, the participants will be asked to discontinue the trial, and the doctor will administer appropriate treatment. Adverse acupuncture events include subcutaneous hematoma, continuous acupuncture afterfeeling, and itching at the sites of needle insertion and will be recorded by the assessors.

**Table 2 Tab2:** Clavien-Dindo classification

**Grade 1**	Any deviation from the normal postoperative course without the need for pharmacologic treatment or surgical, endoscopic, and radiologic interventions. Allowed therapeutic regimens are drugs as antiemetics, antipyretics, analgetics, and diuretics, and electrolytes and physiotherapy. This grade also includes wound infections opened at the bedside
**Grade 2**	Requiring pharmacologic treatment with drugs other than such allowed for grade I complications. Blood transfusions and total parenteral nutrition are also included

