## Discussion

POI is a pathological state that always occurs after colorectal surgery and inflicts a considerable financial burden on patients and society. This trial will evaluate the effects of performing EA at ST25 or ST36 in accelerating the POI recovery time.

Although several trials have been conducted, the consensus [19] is that acupuncture is not a recommended treatment for POI, which may be due to the low reliability of trials. This trial fully meets methodological requirements and achieves full randomization of patients and blinding for patients, hospital staffs, outcome assessors and statisticians.

Actual clinical results show that postoperative patients are more likely to accept acupuncture with fewer acupoints, which can reduce the discomfort caused by acupuncture. Thus, we have chosen ST25 or ST36 as treatment acupoints, which have already been proven to be effective for gastrointestinal dysfunction [35–37]. Our aim is to observe whether EA at a single acupoint can promote recovery from POI.

The pathological state of POI lasts for a maximum of 4 days after surgery [33]. Our intervention will last for 4 days after surgery to ensure that every patient is treated with electroacupuncture during the pathological state. In addition, EA with 2/100-Hz stimulation has been proven to be effective in reducing postoperative incision and visceral pain [38, 39].

A limitation of the trial is that visible acupoints in patients in the two groups receiving acupuncture may break blindness. Another limitation is that as all patients will receive RSPC which is based on a protocol for enhancing recovery after surgery [40], it may lead to a ceiling effect, and the efficacy of electroacupuncture may be negatively affected. However, we hope the trial will provide more reliable evidence than previous studies and clarify the value of electroacupuncture as a treatment for POI.

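### Assessors described as blinded are assigned to record needle-site reactions, and the Discussion claims patient and assessor blinding without the exception that the Abstract and Masking section make

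*Protocol article*

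**What the plan says.** All references are to the protocol article.

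- **Masking:** EA patients, surgeons and nurses are blinded, and so are the next groups listed: "assessors, and statisticians will be blinded to the group assignments, but the patients in the control group will not be blinded". The acupuncturists are unblinded. The Abstract makes the same exception: "Patients in the two electroacupuncture groups, but not in the control group, will be blinded to the group assignments".
- **Secondary outcomes:** adverse acupuncture events are subcutaneous hematoma, persistent afterfeeling and "itching at the sites of needle insertion and will be recorded by the assessors". Assessors also record and grade postoperative complications by Clavien-Dindo.
- **Primary outcome:** times to first flatus and first defecation "will be recorded in hours in the case report form by patients under the supervision of an assessor during hospitalization". The Abstract says: "The outcomes will be assessed by the patients themselves every day during hospitalization".
- **Control group:** "Patients in the control group will receive RSPC without acupuncture". There is no sham needling.
- **Background:** the hypotheses compare either EA arm with control.
- **Discussion:** the trial "achieves full randomization of patients and blinding for patients, hospital staffs, outcome assessors and statisticians". The only blinding limitation it admits is that visible acupoints may unmask patients in the two EA groups.

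**The concern.** Two statements about blinding conflict with other parts of the same document.

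First, a role described as blinded is assigned a task that can unmask it. Hematoma, afterfeeling or itching at a needle site cannot occur in a control patient. The sites also differ between arms (abdomen for ST25, leg for ST36, per Table 1), so one recorded event can reveal the exact arm. The text names no separate, unblinded recorder for these events.

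Second, the Discussion presents patient and assessor blinding as achieved, and hopes the trial will be more reliable than its predecessors. For EA versus control, patients cannot be blinded. EA patients are needled to a felt sensation and receive a current they can perceive, while controls receive neither. Blinding of EA patients can therefore mean only that they do not know whether ST25 or ST36 is the group of interest, and that is not the tested hypothesis. These same patients record the primary times.

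At stake are the supervision of the primary record, the grading of complications, and how far a positive result can be attributed to acupoint stimulation rather than to knowledge of treatment.

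**Working it through.** **Setting the statements side by side**

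| Point | One place | Another place | Consistent? |
|---|---|---|---|
| Assessors | Masking: blinded | Secondary outcomes: record needle-site events | No, for any patient with an event |
| Control patients | Abstract and Masking: not blinded | Discussion: patients blinded, no exception | No |
| EA patients | Abstract and Masking: blinded | Intervention and Control group: EA needled, controls not | Only for ST25 versus ST36 |
| Statisticians | Masking: blinded | Nothing contrary | Yes |

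**How much could knowledge of treatment matter?** The documents give no figure for reporting bias, so this is an illustration with an assumed shift. It covers one EA arm against control and uses a normal approximation for means, as the sample-size section does. The planned test is Breslow.

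*Inputs from the Sample size section:* SD 21.6 h (flatus) and 45 h (defecation); two-sided significance 0.025; 35 per group with 10% dropout, so 35 × 0.9 = 31.5 evaluable per arm. *From Statistical analysis:* the primary outcome counts as different only if both components are significant.

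*Check on the plan's own figure.* For flatus, the difference is 64.8 − 48 = 16.8 h.

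n = 2 × [(2.2414 + 0.8416) × 21.6 / 16.8]² = 31.4, so 32 per arm; 32 / 0.9 = 35.6, so 36. The plan states 35, which is close enough to confirm the inputs.

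*Standard errors.*
- Flatus: 21.6 × √(2/31.5) = 5.44 h
- Defecation: 45 × √(2/31.5) = 11.34 h

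*Chance of a significant result favouring EA with no true effect:* P(Z > 2.2414 − shift/SE). With no shift this is 1.25% per component.

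| Assumed shift | Flatus alone | Defecation alone |
|---|---|---|
| 3 h | P(Z > 1.690) = 4.5% | P(Z > 1.977) = 2.4% |
| 6 h | P(Z > 1.139) = 12.7% | P(Z > 1.712) = 4.3% |

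*Both components significant* (bivariate normal with the same thresholds). The correlation is not in the documents and is assumed.

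| Correlation | No shift | 3 h on both | 6 h on both |
|---|---|---|---|
| 0 | 0.02% | 0.1% | 0.6% |
| 0.3 | 0.08% | 0.4% | 1.3% |
| 0.5 | 0.18% | 0.7% | 2.0% |
| 0.7 | 0.35% | 1.1% | 2.9% |

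At correlation 0 and a 6 h shift, the joint figure is the product 0.127 × 0.043 = 0.0055. At any correlation it cannot exceed the smaller single-component figure, 4.3%.

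**The case against.** The strongest reply has four parts.

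1. **Much of this is disclosed.** The Abstract and Masking section say control patients are not blinded, and the Control group section says they receive no acupuncture. This stands: a reader of those sections is not misled, and the fault on patient blinding lies in the Discussion alone. The absence of a sham is a design choice and is not itself an error.

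2. **Some masking survives.** A reader might infer that the trial has no effective blinding at all. The document does not support that. Statistician masking is untouched, nothing in the event-recording task unmasks surgeons or nurses, and EA patients may still be unaware of the ST25 versus ST36 contrast. A needle-site event unmasks only the patient who has it, and no event rate is given. The daily form is not shown, so one cannot say that its layout breaks the mask; the point rests on the role named in the text.

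3. **The flatus figure is not a trial error rate.** A reader might take 13% as the false-positive risk of the trial. The both-components rule rules that out: the joint figure under the same assumption is 0.6% to 2.9%. First flatus and first defecation are discrete events timed under supervision, and nothing in the document suggests a systematic 6 h error. The choice of 6 h, half the stated 12 h minimum important difference, is arbitrary.

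4. **Reassigning the form is a partial remedy.** Assessors would still supervise patients who know whether they were needled, and acupuncturists would report harms of their own treatment. Both are true, and both are reasons to add an instruction to patients and to state the limitation plainly.

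None of this removes the conflict between the Masking and Secondary outcomes sections, or the one between the Discussion and the Abstract and Masking sections.

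**Conclusion.** The point holds in this form: the assessor mask conflicts with the assessors' assigned recording of needle-specific events, and the Discussion overstates patient and assessor blinding for the comparison being tested. Its blinding limitation covers only the two EA groups and omits EA versus control, where there is no sham and the patients recording the primary times know whether they were needled.

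The numerical consequence for the primary conclusion is modest. If both times shifted by an assumed 6 h with no true effect, success favouring EA would rise from between 0.02% and 0.35% to between about 0.6% and 2.9%, for assumed correlations of 0 to 0.7, and never above 4.3%. The rise to about 13% applies to flatus read alone. The shift and the correlation are both assumptions. The firm part of the finding is the textual contradiction, which should be corrected. A claim that all blinding fails, or that the trial's error rate reaches 13%, would go beyond the document.

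**What to change.** 1. **Recording.** Have the acupuncturist, who is already unblinded, or another existing unblinded team member record acupuncture adverse events on a separate form withheld from outcome assessors until database lock. Assessors keep Clavien-Dindo grading and supervision of the primary record.
2. **Conduct.** Instruct patients not to reveal their treatment to assessors.
3. **Discussion.** State that EA versus control is open-label for patients with patient-recorded primary outcomes, and that patient masking applies only to EA A versus EA B. Limit the conclusion to EA plus routine standard postoperative care versus that care alone. Extend the stated limitation accordingly. The Abstract already gives the control exception and needs no change on that point.

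**Cost:** one form, one instruction and a weaker blinding claim, with no additional patients or staff. The small downside is that acupuncturists would report harms of their own treatment; using another unblinded team member avoids this. The change protects the assessor mask only in part, because assessors still meet patients who know whether they were needled.

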**Table 3 Tab3:**
[figure not shown]
Daily assessment form during postoperative hospitalization

*VAS* visual analog scale, *PCA* patient controlled anesthesia

**Fig 2 Fig2:**
[figure not shown]
Schedule of enrollment, intervention, and assessment

### Data management

All data will be collected in case report forms (CRFs) that have been created by study members and will be entered into electronic record form by two independent researchers to ensure the accuracy of the data from the operation day to the discharge day. The investigators will continue to collect data on patients in the ward who have fallen off treatment for as long as possible until the end of the trial (discharge). The data collectors will be trained to fill out the CRFs to ensure the accuracy of the data. Paper files, including the original CRFs (including the baseline data and DSF data) and consent forms, will be kept for more than 5 years after publication. All final data will only be accessed by the study staff and kept strictly confidential. Readers and reviewers who have questions or want to check the original data can contact the corresponding author. Private patient information, including names, home addresses, and telephone numbers, will be kept confidential at all times.

Moreover, an independent Data and Safety Monitoring Board (DSMB) will be set up to review the trial data every month and determine whether the patient needs to discontinue from this trial in the event of complications and seek medical attention. The members of the DSMB are selected and appointed by the sponsor and include physicians and ethicists who are not involved in the study. The role of the DSMB is to help sponsors maintain a rigorous study design, give appropriate attention to subject protection, review and evaluate clinical efficacy and safety data collected during the study, and evaluate cumulative reports of serious adverse events.

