### Sample size

The primary outcome consists of the time to first flatus and the time to first defecation. Based on previous trials [24, 25] and clinical experience, the time to first flatus will be assumed to be 48 h and 64.8 h for the EA group and the control group, respectively, with a standard deviation of 21.6. Given a 2.5% two-sided significance, 80% power, and 10% drop rate, a sample size of 105 patients will be recruited, with 35 patients in each group. The time to first defecation will be assumed to be 86 h and 122 h for the EA group and the control group, respectively, with a standard deviation of 45. Given a 2.5% two-sided significance, 80% power, and 10% drop rate, a sample size of 90 patients will be recruited, with 30 patients in each group. In conclusion, 105 patients, with 35 patients in each group, will be recruited.

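### First defecation, a co-primary time, is recorded only until discharge, and the stated last-observation rule could count discharge as the event for anyone sent home first

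*Protocol article*

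**What the plan says.** All references are to the protocol article.

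- **Primary outcome.** The two times run from the end of the operation and "will be recorded in hours in the case report form by patients under the supervision of an assessor during hospitalization".
- **Data management.** Data are collected "from the operation day to the discharge day". For patients who have stopped treatment, the investigators will "collect data on patients in the ward who have fallen off treatment for as long as possible until the end of the trial (discharge"). That second sentence is a retention provision for one subgroup. The first sentence and the Primary outcome section set the same window for everyone.
- **Sample size.** "The time to first defecation will be assumed to be 86 h and 122 h for the EA group and the control group", "with a standard deviation of 45".
- **Statistical analysis.** The times are compared by the Breslow (generalized Wilcoxon) test at 0.025. Both flatus and defecation must be significant for the primary outcome to count as different. Missing data are to be filled by carrying the last observation forward.
- **Secondary outcomes.** Length of stay is itself an outcome, so the plan allows that it may differ by arm. No expected stay is given.

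**The concern.** The collection window closes at an event, discharge, that the text does not link to the endpoint. On the plan's own figures the endpoint comes late: the control mean plus one SD is 122 + 45 = 167 h, about day 7. The Discussion describes routine care as based on an enhanced-recovery protocol. Anyone who goes home before defecating leaves no defecation time, and no later analysis can supply one.

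Two things are at stake. Discharge probably depends on recovery, so censoring there may be informative. And the only rule stated for missing values has no natural meaning for an event not yet seen. Applied literally, it enters the discharge time as the defecation time, so an effect on length of stay can pass for an effect on defecation. Because both endpoints must succeed, a fault in this one can change the trial's conclusion.

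**Working it through.** **Plan's own figure.** Per group n = 2(z₀.₉₈₇₅ + z₀.₈₀)²(SD/difference)², with (2.241 + 0.842)² = 9.505.

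- Flatus: 2 × 9.505 × (21.6/16.8)² = 31.4; 31.4/0.9 = 34.9, so 35. This matches the plan.
- Defecation: 2 × 9.505 × (45/36)² = 29.7, so 30 evaluable; 29.7/0.9 = 33.0. The stated 30 is thus the number before dropout. The final 35 per group covers it.

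**Share with no defecation by discharge time c.** P(T > c) = 1 − Φ((c − mean)/45), with means 86 and 122 h. For example, at 120 h, EA: (120 − 86)/45 = 0.756, giving 22%; control: (120 − 122)/45 = −0.044, giving 52%. The discharge times are assumptions. The lognormal columns use the same means and SD.

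| Common discharge | EA, normal | Control, normal | EA, lognormal | Control, lognormal |
|---|---|---|---|---|
| 120 h | 22% | 52% | 18% | 45% |
| 144 h | 10% | 31% | 10% | 26% |
| 168 h | 3% | 15% | 5% | 14% |
| 240 h | 0% | 0.4% | 1% | 2% |

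**If stay differs by arm.** With EA discharged 36 h before control, (c − 36 − 86)/45 = (c − 122)/45, so the normal-model shares are equal. With EA at 120 h and control at 168 h they reverse: 22% against 15%.

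**What the analysis then does.** Simulated Breslow test, two-sided 0.025, 31 evaluable per arm (35 × 0.9 = 31.5), lognormal defecation times, discharge SD 36 h (assumed), discharge unrelated or moderately positively related to defecation.

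*Plan's assumed effect, mean discharge 120 h in both arms:*

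| Handling | Power |
|---|---|
| Followed to the event | about 0.89–0.90 |
| Censored at discharge | about 0.92–0.94 |
| Discharge carried forward as the event | about 0.75–0.79 |
| Patient dropped | about 0.67–0.74 |

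A separate run with independent discharge gave 0.91 for full follow-up, 0.91 censored, 0.81 carried forward and 0.74 dropped. In that run the 36 h difference shrank to about 23 h under carry-forward. At mean discharge 168 h the last three powers were 0.91, 0.90 and 0.88, so the problem fades as stay lengthens.

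*No effect on defecation, mean stay 120 h in EA and 144 h in control:* the false-positive rate is about 0.03–0.035 if censored and about 0.10–0.15 if discharge is carried forward, against the nominal 0.025.

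Power levels depend on the assumed shape. With normal times they are all lower and censoring itself costs some power, but carry-forward and dropping remain the worst choices.

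**The case against.** The strongest reply is that nothing shown says patients leave before defecating. No length of stay, minimum stay or discharge criterion is given. A condensed article may leave these to the full protocol, and the daily form and the schedule figure are not shown. If the ward in practice discharges only after defecation, the loss is nil. Very early discharge is also unlikely: EA runs for four days from the first postoperative day, and even sips of water wait for first flatus, assumed at a mean of 64.8 h in controls. All of this stands, so the size can be given only as a conditional range.

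A reader might infer that controls necessarily lose the endpoint more often. The documents do not support that: it requires similar discharge times in the arms, and the imbalance vanishes or reverses if EA shortens stay.

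A reader might also infer that stopping at discharge by itself destroys power. The named test accepts censored times, and in the simulation above censoring keeps power. Nor can the largest shares and strongly informative censoring both be claimed at once. The closer discharge follows bowel recovery, the fewer patients leave without the event.

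What survives is that the text never says these patients will be censored, while it does state a fill rule that conflicts with censoring. A statistical analysis plan could mend the rule, but it could not supply times that were never collected.

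**Conclusion.** The point holds in conditional form. The recording window can miss a co-primary time, and the stated missing-data rule handles such a miss badly. With a common discharge time the share without an event runs from 22% (EA) and 52% (control) at 120 h to about nil by 240 h. The main damage comes from carry-forward or from dropping patients. At an assumed mean discharge of 120 h, power is about 0.75–0.79 or 0.67–0.74 respectively, against about 0.90 with full follow-up. If EA shortens stay without affecting defecation, carry-forward produces false positives at about four to six times the nominal rate (0.10/0.025 = 4; 0.15/0.025 = 6).

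These figures rest on the plan's means and SD, an assumed lognormal shape for the simulations, and assumed discharge times. They do not show that any patient will in fact be discharged first. The change is worth making because it is cheap and protects an endpoint on which success depends.

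**What to change.** - **Primary outcome and Data management:** collect time to first defecation until the event or a fixed cap chosen by the sponsor. A patient discharged first takes the form home and gets a scripted call; form, script and timing are identical in all arms.
- **Statistical analysis:** exempt the two primary times from last-observation carry-forward. Treat a patient without the event at the cap, or at loss of contact, as censored at that time.

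The cost is a short amendment and a few calls by existing staff. The downside is that these times are self-reported at home without assessor supervision, by patients of whom the controls are unblinded. Recording whether each time was obtained in hospital or by call would show how much of the comparison rests on home reports.
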